### Participants

Fifteen SUs and, from a minimum of 4 to a maximum of 8 staff members, will be recruited from WDP. In total, we will recruit between 19 and 23 participants. The inclusion criteria for the recruitment of SUs include: (I) being a SU in structured treatment for drug and/or alcohol misuse, (II) being 18 years old or older, (III) reporting symptoms of depression and/or anxiety, (IV) being deemed suitable to take part in a group/individual setting by their key workers (who are Recovery Practitioners responsible for coordinating and delivering psychosocial interventions for SUs), (V) being right-handed.

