The exclusion criteria for the recruitment of SUs include: (I) having a legal requirement to attend as part of a Drug Rehabilitation Requirement or Alcohol Treatment Requirement as this may impact engagement results, (II) being unable to provide informed consent due to a lack of mental capacity, (III) little/no understanding of spoken English as all sessions will be carried out in English and instructions for subjective measures used in this project are in English, (IV) being left- and mixed-handed: an outcome measure utilized (i.e., the EEG frontal alpha asymmetry) is modulated by handedness direction (i.e., left-handed, right-handed) providing empirical justification for the practice of excluding left-handers and mixed-handers when exploring relationships between this neural marker and other variables [34], (V) not being registered with a general practitioner (GP)/unable to provide GP details: we will require GP details to notify them in case of any incidental EEG findings. Furthermore, participants who disclose in the consent form that they had experienced a Stroke, Traumatic Brain Injury, or Epilepsy will be contacted by the research team to discuss if they can wear an EEG cap and participate in the measurements. Our inclusion and exclusion crit﻿eria are broadly based on the eligibility criteria for SUs to attend most groups in the service. We expect participants to either be abstinent or present with low to moderate substance use. Participants would also likely be housed and have access to public funds. While this presents a sample with diverse substance use patterns and individual circumstances, this is more representative of the cohort that would use this type of intervention. The diversity in participants may aid determining feasibility and acceptability of the intervention and provide value in planning further more focused studies. Regarding SG, only members of WDP staff will be included in this group.

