### Procedure

One week prior to the start of the interventions, the baseline measurement battery (secondary outcomes) will take place. Handedness will be assessed with the Edinburgh Handedness Inventory and a pre-EEG screening questionnaire will be administered. 

This includes questions about SU use of alcohol or any other substances, previous episodes of Stroke, Epilepsy, Brain Injury, or other conditions that may make wearing a cap or head garments difficult, uncomfortable, or painful. Furthermore, we will ask if participants are currently prescribed any antipsychotic, anti-depressive, or anti-anxiety medication. Quantitative and qualitative data will be collected through the outcome measuring tools (Table 1).

**Table 1 Tab1:** Representation of primary and secondary outcomes, their labels and timepoints of administration

Outcome	Measure label	Measure timepoints
Primary outcome		
Feasibility and acceptability	Participant satisfaction survey	At Week 8
	Attendance sheet	After each session
	Exit questionnaire	Following disengagement with intervention
	Focus group	At Week 9
Secondary outcomes		
Substance use (a) Days of primary substance used (b) Usage of primary substance per day Physical Wellbeing Mental Wellbeing Overall Quality of Life	Treatment Outcome Profile (TOP)	Baseline and Week 8 (end of treatment)
Retention in treatment completion rate	WDP Case management system	At week 11
Substance craving	Brief Substance Craving Scale (BSCS)	Baseline and week 8 (end of treatment)
Neural correlates of substance craving	Beta frequency band/resting state	Baseline and week 8 (end of treatment)
Levels of depressive symptoms	Patient Health Questionnaire–9 (PHQ-9)	Baseline and week 8 (end of treatment)
Neural correlates of depressive symptoms	FAA/resting state	Baseline and week 8 (end of treatment)
Levels of anxiety	Generalised Anxiety Disorder–7 (GAD–7)	Baseline and week 8 (end of treatment)
Neural correlates of anxiety symptoms	FMT/resting state	Baseline and week 8 (end of treatment)
Inhibitory control	Visual behavioral Go/No-Go task	Baseline and week 8 (end of treatment)
Neural correlates of inhibitory control	EEG event-related potential (ERP) P3	Baseline and week 8 (end of treatment)
Therapeutic alliance	The Helping Alliance Questionnaire–II	After IMT session 2 and 5
Moments of therapeutic interest	Semi-structured Interview	After IMT session 2 and 5
	Audio-visual data	During IMT session 2 and 5

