### Analysis strategy regarding the secondary study aims

The strategy for the secondary aims entails data collection and analysis of quantitative and qualitative data from the EEG, questionnaires, a behavioral task, and a semi-structured interview. To analyze the effects of an MT program (GMT/IMT) in addition to ST compared to ST only on secondary dependent variables, descriptive, graphical, and inferential analyses will be used. Effect sizes will also be computed where relevant. The present research is a feasibility study and because of the small sample size, certain inferential statistics requirements cannot be satisfied. Therefore, results related to the secondary aims are to be considered—and will be presented as—preliminary. Descriptive analyses will be conducted by calculating means and standard deviations at each time point. Inferential statistical analyses will be conducted to evaluate the effect of MT (GMT/IMT) in addition to ST on mental health and brain processing by comparing the data between pre- and post- intervention in each group using a parametric or non-parametric test (e.g., paired t-test or Wilcoxon Signed-Rank test, respectively) depending upon the data distribution. The dependent variables that we will measure are pre-post intervention changes in the following outcomes: (I) score of the PHQ-9 and resting-state FAA for depressive symptoms; (II) score of the BSCS and resting-state beta frequency band for the craving state experienced over a 24-h period; (III) score of the GAD-7 and resting-state FMT for anxiety symptoms; (IV) score of the TOP for substance use, days of primary substance used, average usage of primary substance per day, physical wellbeing health, psychological health, and overall quality of life; and (V) P3 EEG event-related potential amplitude and behavioral accuracy during a Go/No-Go task for the inhibitory control. The statistical procedure to analyze data from pre-post intervention questionnaires involves both within-subject (or repeated-measures design) and between-groups (or independent design). Indeed, a pre-post intervention comparison of scores from the questionnaires will be performed for each group (GMT, IMT and ST) with a paired-samples t-test. In case the assumptions of normality and homogeneity of the data will be violated, a non-parametric Wilcoxon Signed-Rank test will be performed. The difference scores obtained from this repeated-measures design, will be used for the independent design analysis: pre-post intervention difference scores in the questionnaires administered to the MT groups (GMT and IMT) will be compared with pre-post intervention difference scores in the questionnaire administered to the ST group utilizing independent t-test. In case the assumptions of normality and homogeneity of the data will be violated, a non-parametric Mann–Whitney test will be performed.

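### Raw daily amount of each person's primary substance is pooled across alcohol and drug users with no common unit, so its mean, tests and effect size depend on the recording unit

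*Protocol article*

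**What the plan says.** Under Analysis strategy regarding the secondary study aims, the dependent variables taken from the Treatment Outcome Profile (TOP) include "score of the TOP for substance use, days of primary substance used, average usage of primary substance per day". Table 1, under Procedure, lists "Usage of primary substance per day" as an outcome in its own right, separate from days of use, at baseline and week 8.

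The same analysis section sets one general treatment for these variables:
- Description: "Descriptive analyses will be conducted by calculating means and standard deviations at each time point".
- Within group: "a pre-post intervention comparison of scores from the questionnaires will be performed for each group (GMT, IMT and ST) with a paired-samples t-test", with the Wilcoxon signed-rank test if assumptions fail.
- Between groups: the difference scores of the music therapy participants "will be compared with pre-post intervention difference scores in the questionnaire administered to the ST group utilizing independent t-test", with the Mann–Whitney test if assumptions fail.
- Effect sizes are to be computed where relevant.

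The Participants section admits anyone "being a SU in structured treatment for drug and/or alcohol misuse". It adds that "this presents a sample with diverse substance use patterns and individual circumstances" and treats this as an advantage for judging feasibility. The article gives no common unit, conversion, within-person scaling or split by substance for the daily amount.

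**The concern.** The item is an amount of whatever each person mainly uses. An amount of alcohol and an amount of a drug do not share a scale, so a mean or SD across them combines unlike quantities, and so does a difference in means. Rescaling one substance, for example from grams to milligrams, leaves everyone's consumption the same but changes the pooled statistics. Even the sign of the pooled change can reverse.

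Substance use is the first treatment outcome named under the secondary objectives. The article expects the TOP to give indicative results for later studies, and it presents the trial as groundwork for a larger randomised trial. A direction or effect size that depends on the recording unit could be carried into that planning.

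**Working it through.** The article states no SD, effect size or power figure for this item, so there is no figure to reproduce. Two checks can be made.

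**1. Does the planned result depend on the unit?**

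All values here are assumed, because the article gives neither units nor substance mix. Take one arm of five, the planned arm size.
- Three drinkers, units/day: 8, 6, 10 before; 6, 5, 8 after.
- Two drug users, g/day: 0.5, 1.0 before; 0.8, 1.3 after.

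Formulas: d = after − before; t = mean(d) / (SD(d)/√5).

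*Drug in grams.* d = −2, −1, −2, +0.3, +0.3.
- Mean change = (−5 + 0.6)/5 = −0.88; SD(d) = 1.15; t = −1.71.
- Pooled means: 5.1 (SD 4.2) before, 4.2 (SD 3.1) after.

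*Drug in milligrams, same people and same consumption.* d = −2, −1, −2, +300, +300.
- Mean change = (−5 + 600)/5 = +119; SD(d) = 165.2; t = +1.61.
- Pooled means: 304.8 (SD 443.2) before, 423.8 (SD 598.4) after.

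*Wilcoxon fallback.* It ranks absolute differences across participants.
- Grams: 0.3 and 0.3 share rank 1.5, 1 has rank 3, and 2 and 2 share rank 4.5. W+ = 1.5 + 1.5 = 3; W− = 3 + 4.5 + 4.5 = 12.
- Milligrams: 1 has rank 1, 2 and 2 share rank 2.5, and 300 and 300 share rank 4.5. W+ = 4.5 + 4.5 = 9; W− = 1 + 2.5 + 2.5 = 6.

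*Mann–Whitney fallback.* It ranks the same raw differences between groups. A drinker's change of −2 lies below a drug user's change of −0.3 g, but above the identical change written as −300 mg. The order therefore also depends on the unit.

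*Unit-free summary.* Three of five decreased and two increased, in either unit.

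**2. Could everyone share one unit by chance?**

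Assume two unit classes, with a share p of the service in the larger one and participants drawn independently. The chance that all n fall in one class is p^n + (1 − p)^n.

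| Assumed p | All 15 participants | All 5 in one arm |
|---|---|---|
| 0.50 | 0.006% | 6.3% |
| 0.70 | 0.5% | 17% |
| 0.80 | 3.5% | 33% |
| 0.90 | 21% | 59% |
| 0.95 | 46% | 77% |

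A single arm may escape by chance, which would spare its within-group test. The whole sample is unlikely to escape unless one class dominates the service.

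**The case against.** The strongest reply is that the article never states the recording unit or the substance mix. How the TOP records or scores the amount lies in the instrument, which is not shown. That stands: differing units are an inference from the eligibility rule and the authors' own expectation of diversity. A reader might infer that the article declares mixed units and that the average is certain to be meaningless. It does not say so, and the point is conditional.

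A second reply is that item-level handling belongs in a fuller document. This carries less weight. The article names the variable, the summary and the tests, and makes no exception for this item. The difficulty comes from applying the stated rule as written.

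A reader might also infer that the arm difference would mainly show which arm holds more users of the large-unit substance. The planned comparison does not support that. It uses change scores, so a large-unit user whose consumption does not change contributes zero. What remains is narrower: the comparison is weighted toward changes among large-unit users. Nor is a falling mean that hides some increases evidence of the defect, since that can happen when all participants drink and share one unit.

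Finally, the item is one part of a small feasibility study whose secondary results are labelled preliminary. That limits the impact. However, the label warns of imprecision, and a larger sample would not cure a problem of units.

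Abstinent participants contribute zeros, which carry no unit. They do not make the other amounts comparable.

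**Conclusion.** The point holds in conditional form. Unless all participants share one primary substance and unit, the pooled mean, SD, t-tests, both rank-test fallbacks and any effect size for average daily usage depend on an arbitrary choice of unit. In the assumed arm the mean change moves from −0.88 to +119 and the direction reverses. These values show what can happen and do not predict the trial's result.

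The defect is confined to this one item. Days of primary substance used is on a common scale, and the other TOP items are not affected by mixed substance units. Because the item is secondary and preliminary, and the primary outcomes are feasibility and acceptability, the impact is modest. The correction is still worth making because it is cheap.

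**What to change.** In Analysis strategy regarding the secondary study aims, exclude raw daily amount from pooled means and SDs, t-tests, rank tests and effect sizes. Report it in two ways instead:
- a listing per participant, with substance, unit, baseline and week 8 amount;
- the number in each arm who decreased, were unchanged or increased.

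The count copes with zero baselines, which matters because abstinent participants are expected and a percentage change from zero is undefined. Show participants without a week 8 TOP separately, since the carry-forward rule under Sample size and dosage would otherwise count them as unchanged.

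Keep days of primary substance used as the substance-use measure for group-level quantitative comparison. It need not become the only substance-use outcome.

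The cost is a change of wording and the loss of one raw-amount summary. No new assessment is needed, provided the substance and unit are recorded with each amount.

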**Methods:**

Fifteen participants, from a community service based in London, will take part in a mixed-methods non-blind randomized-controlled trial. Ten participants will receive six-weekly sessions of music therapy in addition to the standard treatment offered by the CSMTS—five of them will receive individual music therapy and five of them will receive group music therapy—while a further five participants will act as a control group receiving standard treatment only.

Satisfaction and acceptability will be evaluated in focus groups with service users and staff members following the final treatment session. Moreover, attendance and completion rates will be monitored throughout the intervention. Subjective and behavioral indexes will be assessed before and after the interventions to explore the effects of music therapy on craving, substance use, symptoms of depression and anxiety, inhibitory control, and will be correlated with associated neurophysiological signatures. In-session analysis of two individual music therapy sessions will serve to explore how music and emotion are processed in the brain within the therapy. The data collected at each step will be included in an intention-to-treat analysis basis.

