The staff cohort will be recruited by directly approaching staff members who were involved in the project or may be involved in future forms of the program. This will be done by emailing them directly or attending staff meetings and asking for volunteers to participate. Staff members will also be invited to attend the drop-in session. SUs who participate will be rewarded Capital Card^®^ points. Points will be awarded for each session completed, including the focus group and interview. WDP Capital Card^®^ is a reward card scheme to help SUs with their recovery journey ([35]; https://www.wdp.org.uk/the-capital-card). Where the project has issues recruiting the full number of 15 SU participants, we will extend the recruitment window to 2–3 months and we will re-run the drop-in session to attract more SUs. We will also contact WDP key workers to promote the study. Recruitment for GMT will continue until 5 participants are recruited and allocated to this group. If the 5 participants are not recruited within 2 months, the GMT sessions will start once at least 3 participants have been allocated. The GMT will continue while 3 participants remain in the study. The start of the IMT sessions will be staggered: SUs allocated to the IMT group will start their MT sessions within 1–2 weeks of being allocated to this group. If a participant in the IMT group drops out within the first 2 weeks, we will re-recruit and the new participant will start from week 1. We will only re-recruit twice before continuing with the remaining IMT participants. If after 3 months, the project does not have enough participants to go ahead, the research team will discuss additional recruitment strategies, widening the inclusion/exclusion criteria or a possible change in study location. The research team will take any feedback from SUs or staff around recruitment and incorporate where necessary. Where a participant decides to withdraw from the study, they will be provided an exit survey and withdrawal confirmation form. This form gives the participant the option to decide if the data collected up to their withdrawal will be kept and used in the final analysis or destroyed and not used in the final analysis. If they choose not to complete this survey or ask that all their data collected up to their withdrawal is deleted, the exit survey will be destroyed.

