
For the resting-state EEG data (alpha—FAA -, beta, and theta—FMT—bands) pre-post intervention comparisons will be performed utilizing z-scores from a Normative EEG database (NG software) [54]. Furthermore, to represent the pre-post intervention difference in the topographic distribution of EEG power in the selected frequency bands a paired-samples t-test will be performed for each of the three groups. If deviations from normality will be found in the data, a non-parametric Wilcoxon Signed-Rank test will be performed. Between-group power differences will be calculated as well, by comparing differences in the topographic distribution of the EEG power in participants who received MT (GMT and IMT) alongside ST vs participants who received ST only through an independent t-test. If deviations from normality will be found in the data, a non-parametric Mann–Whitney test will be performed. Relationships between changes in the pre-post intervention questionnaire scores (PHQ-9, GAD 7, BSCS, VAS, HAQ-II) and changes in the respective EEG measures (see above) will be tested using Pearson's correlation coefficients with 95% confidence interval [16]. Likewise, we will implement the same correlation procedure to test the relationship between pre-post intervention changes in inhibitory control (P3 ERP amplitude and accuracy on “no-go” trials) and changes in the scores of the Brief Substance Craving Scale. Changes in the pre-post MT (GMT and IMT) sessions scores from the craving thermometer will be analyzed graphically (i.e., scatterplot). Those who attend more than two sessions but disengage before the study ends will have the measures up to the point of their disengagement included in data analysis.

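### The questionnaire rule makes homogeneity a condition of the paired t-test, which does not need it, and the EEG rule for the same test does not ask for it

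*Protocol article*

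**What the plan says.** The abstract fixes the arms: "five of them will receive individual music therapy and five of them will receive group music therapy", and "a further five participants will act as a control group receiving standard treatment only".

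The section *Analysis strategy regarding the secondary study aims* describes the choice of paired test three times:

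- In general terms, a paired t-test or a Wilcoxon signed-rank test is used "depending upon the data distribution". Variance is not mentioned.
- For questionnaires, "a pre-post intervention comparison of scores from the questionnaires will be performed for each group (GMT, IMT and ST) with a paired-samples t-test". The switching rule follows: "In case the assumptions of normality and homogeneity of the data will be violated, a non-parametric Wilcoxon Signed-Rank test will be performed".
- For resting-state EEG power, again a paired t-test in each of the three groups: "If deviations from normality will be found in the data, a non-parametric Wilcoxon Signed-Rank test will be performed".

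The questionnaire rule then appears again in the same form for the independent t-test on difference scores, with Mann–Whitney as the fallback. The section also says that small numbers prevent some inferential requirements from being met, and that secondary results will be presented as preliminary.

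**The concern.** A paired t-test is a one-sample test on the differences. Its distributional condition is that those differences are roughly normal. Equal variance between two sets of scores is a condition of the pooled independent t-test, so the questionnaire rule attaches it to the wrong test. The questionnaire and EEG results are later correlated with each other (PHQ-9 change with FAA change, for example), yet the same paired test is to be dropped on different grounds in the two domains.

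The direction of the effect also matters. Symptom scores that fall towards zero tend to become less spread. A variance condition can therefore be met or missed because of a treatment response, which has no bearing on whether the paired t-test is valid. The fallback is a coarse test at five pairs.

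**Working it through.** The protocol article gives no alpha, power or p-value for these tests, so there is no planned figure to reproduce. An SD, a correlation and an effect size have to be assumed.

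**1. What the paired t-test uses.** With d = week 8 − week 1, t = mean(d) / (SD(d)/√n). The variance of d is σ₁² + σ₈² − 2ρσ₁σ₈. Whatever σ₁ and σ₈ are, this is one number, and SD(d) estimates it directly. Equality of σ₁ and σ₈ does not enter.

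**2. The Wilcoxon floor.** With n untied, non-zero differences all of one sign, the exact two-sided p is 2/2ⁿ.

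- n = 5: 2/32 = 0.0625. Exact one-sided: 1/32 = 0.031.
- n = 5, normal approximation: mean 5×6/4 = 7.5, variance 5×6×11/24 = 13.75, SD 3.708. z = 7.5/3.708 = 2.023, p = 0.043. With continuity correction z = 7.0/3.708 = 1.888, p = 0.059.
- n = 3: 2/8 = 0.25. *Recruitment* allows this size, since "the GMT sessions will start once at least 3 participants have been allocated".
- n = 6: 2/64 = 0.031. *Recruitment* leaves room for extra IMT participants ("We will only re-recruit twice before continuing with the remaining IMT participants"), but one whose baseline is carried forward has a difference of zero and adds no sign information.

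**3. Does the variance condition protect the error rate, and how often would it act?** Simulation with n = 5 pairs, normal scores, correlation 0.5, 40,000 runs per setting. The check compares week-1 and week-8 scores at the 5% level. All of these settings are assumed.

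| SD week 8 / SD week 1 | Paired-t type I error | Mean-centred Levene flags | Median-centred Levene flags |
|---|---|---|---|
| 1 | 4.9% | 5% | 0.4% |
| 1/2 | 5.0% | 19% | 2% |
| 1/3 | 5.0% | 36–37% | 7% |
| 1/4 | 5.1% | 48–49% | 12–13% |

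With a mean fall of 1.5 baseline SD, the share of all arms that are flagged by the mean-centred check and have paired-t p < 0.05 is 0.194 × 0.706 = 0.137, 0.364 × 0.739 = 0.269 and 0.488 × 0.741 = 0.362 for ratios 1/2, 1/3 and 1/4. With the median-centred check it is 0.015, 0.047 and 0.086.

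**4. Power.** A variance-ratio F-test was used as the trigger, with the exact two-sided Wilcoxon as fallback, week-1 SD 5, a mean fall of 7 and correlation 0.5. Power at 0.05 goes from 0.77 to 0.67 when the week-8 SD is 2.5, and from 0.75 to 0.39 when it is 1.5.

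**5. One invented arm.** Week 1: 20, 16, 12, 9, 14. Week 8: 7, 6, 5, 5, 6. The differences are 13, 10, 7, 4, 8, with mean 8.4 and SD 3.36. t = 8.4/(3.36/√5) = 5.59, p = 0.005, and a Shapiro test of the differences gives p = 0.99. The variances are 17.2 and 0.70, a ratio of 24.6, which an F-test on 4 and 4 df flags. Mean-centred Levene gives p = 0.057 and does not flag. If the arm is switched, the exact two-sided Wilcoxon p is 0.0625 and the uncorrected approximation 0.043.

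**The case against.** The best defence is that this is one misplaced word with little consequence. Five arguments support it.

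- Read literally, the rule needs normality and homogeneity both to fail. Narrowing alone would then switch nothing, and the extra condition would make switching rarer. This reading is open. It removes the power loss but still treats homogeneity as an assumption of the paired test.
- No variance check is named, so the trigger rates above describe checks supplied for this calculation. This stands, and the gap between the two Levene versions shows how much depends on it.
- The Wilcoxon floor is not caused by the homogeneity condition. It applies equally when non-normality triggers the switch, as in the EEG rule. This stands: the correction closes one route to the floor and leaves the other.
- The EEG rule also omits homogeneity for its independent t-test, where it would belong. The contrast may therefore be loose drafting and not two deliberate policies. That is plausible, but the written rules still differ.
- Means, SDs, graphs and, where relevant, effect sizes are reported anyway, feasibility is the primary aim, and no decision hangs on a within-arm p-value. This limits the importance without making the rule right.

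**Conclusion.** The point holds as a rule stated wrongly, and it is minor. That homogeneity is no assumption of the paired t-test, and that the questionnaire and EEG rules differ, rest on no numerical assumption. The possible harm is conditional. It needs the either-fails reading, a week-1 against week-8 variance check, five informative pairs and an exact two-sided p judged at 0.05.

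A reader might infer that a successful treatment automatically pushes an arm into a test that cannot be significant. The document does not support that. It fixes neither the check, nor alpha, nor sidedness, nor exact against asymptotic p-values. Those details may sit in an analysis plan that is not shown, and their absence is not part of this point. Even under the assumed SD ratios of 1/2 to 1/4, most arms are not switched.

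**What to change.** In *Analysis strategy regarding the secondary study aims*:

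- Delete homogeneity from the rule for the paired questionnaire tests only.
- Say that the quantity examined is the within-person difference.
- Apply the same paired rule to questionnaires and EEG.
- Report the mean change with its 95% CI whichever test is shown.
- Keep any variance condition for the independent comparison of difference scores.

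The cost is about one sentence of text. Nothing changes in the design, the data collected or the care given.

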### Interventions

MT involves the use of sounds and music within an evolving relationship between participants and therapist to support and encourage physical, mental, social, emotional, and spiritual wellbeing. Sessions will be delivered by a qualified music therapist, registered with the UK regulator for health and care professions, the Health and Care Professions Council (HCPC). Registered music therapists must have undergone training through an accredited Music Therapy training course, which is offered in the UK either in the form of a two year full time or three year part time masters level training (accredited by the HCPC).

MT sessions will be based upon musical improvisation, composing and writing songs, analyzing lyrics of preferred songs, singing and talking. Participants are not required to have any previous instrument or other music experience. During GMT, active and passive music activities will be conducted as a group. During MT sessions participants will be introduced to a range of both electronic and acoustic instruments, including tuned and untuned percussion, from which they can choose to play and improvise freely. The music therapist will accompany participants in the improvisation. This form of improvisation, with the support of the music therapists, provides participants with an opportunity to connect with emotions and feelings connected to unconscious material. Following improvisations, the therapist and SU may identify moments of interest which can be further explored either verbally or through further improvisation. Utilizing Electronic Music Production Instruments (EMPIs) provides participants with additional creative opportunities while utilizing contemporary timbres and music making techniques, thus offering participants a way to explore their musical and cultural identities [36]. The use of EMPIs also enables the recording of the music created in the sessions, which in turn provides dual benefits: firstly, participants can, if they wish, take a copy of the music they created away, and secondly, the recording can be used in the analysis of sessions.

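### The between-group questionnaire test ignores baseline, and its Mann–Whitney fallback does not cure unequal variances at 10 v 5

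*Protocol article*

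**What the plan says.** The Abstract describes the design: "Fifteen participants, from a community service based in London, will take part in a mixed-methods non-blind randomized-controlled trial". Of the ten allocated to MT, "five of them will receive individual music therapy and five of them will receive group music therapy"; the other five are controls on ST.

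Under 'Analysis strategy regarding the secondary study aims', the between-group step for the questionnaires reads "pre-post intervention difference scores in the questionnaires administered to the MT groups (GMT and IMT) will be compared with pre-post intervention difference scores". The comparator is the control arm on ST, and the test is an unpaired t-test. The fallback is: "In case the assumptions of normality and homogeneity of the data will be violated, a non-parametric Mann–Whitney test will be performed".

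A parallel MT v ST test is planned for resting-state EEG: "Between-group power differences will be calculated as well, by comparing differences in the topographic distribution of the EEG power". It is also an independent t-test, but its Mann–Whitney switch is triggered by non-normality only.

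'Outcome measures for each participant' and Table 1 have all three groups completing the questionnaires, EEG and Go/No-Go task at baseline and week 8. The analysis section warns that some requirements of inferential statistics cannot be met at this sample size, and that secondary results will be presented as preliminary.

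**The concern.** Two separate choices are fixed here, and both can be improved without new data.

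1. **Baseline is used only by subtraction.** A change score assumes that each unit of baseline difference carries over fully to week 8. When the pre-post correlation is well below 1, this over-corrects chance imbalance and adds noise. With 15 people, chance imbalance is not small.

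2. **The remedy for unequal variances does not do that job.** Mann–Whitney is a reasonable response to non-normality. As a level-5% test of no average difference it still relies on similar spread in the two groups, and unequal group sizes make departures from this matter.

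At stake are the precision and the error rate of the preliminary MT v ST estimates and effect sizes. The Conclusion hopes the study will form an empirical base for a larger trial.

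**Working it through.** **Inputs from the protocol article.** 5 individual MT + 5 group MT + 5 ST; both MT groups set against ST; change scores; independent t-test; Mann–Whitney fallback. The article gives no alpha, SD, effect size or pre-post correlation for this contrast, so there is no figure to reproduce.

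**Assumptions.** MT arms pooled (10 v 5), two-sided alpha 0.05, normal data, equal SDs at baseline and week 8 (set to 1), correlation rho from 0.3 to 0.9, SD ratio between arms from 1 to 3.

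**Step 1: chance imbalance.** The SD of the baseline difference between arms is sqrt(1/10 + 1/5) = sqrt(0.3) = 0.55 SD. An imbalance of that size moves the change-score contrast by (1 − rho) × 0.55, which is 0.27 SD at rho = 0.5.

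**Step 2: precision.**
- Variance of the change-score contrast: 2(1 − rho) × 0.3
- Variance of the ANCOVA contrast: (1 − rho²) × 0.3 × (1 + 1/11), where the last factor is the cost of estimating the slope at N = 15

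| rho | change score | ANCOVA | ratio | power for a 1-SD effect, change v ANCOVA |
|---|---|---|---|---|
| 0.3 | 0.420 | 0.298 | 1.41 | 30% v 40% |
| 0.5 | 0.300 | 0.245 | 1.22 | 40% v 46% |
| 0.7 | 0.180 | 0.167 | 1.08 | 58% v 61% |
| 0.8 | 0.120 | 0.118 | 1.02 | 76% v 77% |
| 0.9 | 0.060 | 0.062 | 0.96 | 96% v 95% |

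Break-even: 2(1 − rho) = (1 − rho²) × 12/11, so 1 + rho = 22/12 and rho = 0.83. The power column comes from 20,000 simulated trials per row, whose variances agree with the formulas. ANCOVA type I error with equal variances was 4.8–5.0%.

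**Step 3: error rate of the planned test and its fallback.** Change scores, 10 v 5, no true difference, 20,000 simulated trials per setting:

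| SD ratio | Student t | Mann–Whitney alone | t switching to Mann–Whitney | Welch |
|---|---|---|---|---|
| equal | 5.2% | 4.1% | 5.2% | 5.2% |
| ST 2× MT | 11.9% | 7.0% | 11.2% | 5.5% |
| ST 3× MT | 16.1% | 8.3% | 13.4% | 5.5% |
| MT 2× ST | 2.2% | 2.5% | 2.2% | 4.8% |
| MT 3× ST | 1.5% | 2.2% | 1.4% | 4.5% |

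The switch column assumes a median-centred Levene test at 5%, since the article names no check. That test detects a twofold SD difference in 13% of trials, so the switch seldom operates and the result stays close to the Student t.

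**Step 4: does ANCOVA by itself solve Step 3?** No. At rho = 0.5 with ST 2×/3× as variable, type I error is about 11–12% / 15–18% for ordinary ANCOVA and 8–9% / 9–11% with HC2 standard errors. With HC3 it is about 5.5% / 6–7%. The ranges cover two set-ups: only the residual spread differs between arms, or the whole scale does. With equal variances HC3 gives about 4%, and with MT the more variable arm about 3–4%.

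**The case against.** - **The analysis is secondary and already caveated.** This is true: the primary aim is feasibility, and no decision rests on this test. The caveat concerns sample size, however. It does not justify a less precise estimator or a fallback that misses its purpose.
- **A change score is a recognised, unbiased estimator under randomisation.** This stands. The loss is of precision, it depends on an unstated correlation, and it disappears above about 0.83.
- **The error inflation is assumed and runs one way.** This also stands. Nothing in the article suggests that ST will be 2–3 times as variable. If MT is the more variable arm, the plan is conservative.
- **The t-test might be the Welch form.** The article does not say. Naming homogeneity as an assumption whose failure rules the test out points to the equal-variance form.
- **Pooling to 10 v 5 is inferred.** It is the natural reading, not an explicit one. At 5 v 5 with an SD ratio of 2, error is near nominal (t 5.5%, Mann–Whitney 3.7%).

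Stronger readings that the article does not support:
- A reader might infer that this is the trial's only randomised comparison. It is not: EEG power is also tested between MT and ST, and individual and group MT are compared descriptively on feasibility.
- A reader might infer that a planned confidence interval is too wide. None is stated for this contrast.
- A reader might infer that members of the one therapy group ("During GMT, active and passive music activities will be conducted as a group") invalidate the test through shared outcomes. The article gives no intraclass correlation, and a single group cannot estimate one. At an assumed 0.1–0.2 the pooled SE would rise by only 3–6%.

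**Conclusion.** The point holds as a correctable weakness in a secondary analysis. The unadjusted change score gives up precision for any pre-post correlation below about 0.83, substantially at 0.3–0.5 and slightly at 0.7–0.8. Using Mann–Whitney for unequal variances leaves error off nominal with unequal arms: above 5% if the five-person ST arm is the more variable, below it if MT is. The criticism concerns the homogeneity trigger only, not the use of Mann–Whitney for non-normality. The sizes rest on the pooled 10 v 5 reading, normal data, and correlations and SD ratios that the article does not supply. The feasibility conclusions are unaffected.

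**What to change.** 1. For each questionnaire and each scalar EEG or behavioural outcome, replace the between-group change-score t-test by ANCOVA of the week-8 value on arm and that outcome's own baseline. Report the estimate with a 95% CI, labelled preliminary.
2. Specify HC3 standard errors from the outset, not after a variance pre-test. If change scores are kept, specify the Welch t-test from the outset.
3. Remove Mann–Whitney as the response to unequal variances.

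**Cost.** A change of analysis wording and one residual degree of freedom (13 to 12; critical t 2.160 to 2.179). HC3 is slightly conservative when variances are equal (about 4%), and there is a small loss of precision if the correlation exceeds about 0.83. No extra data or participants are needed.
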